**Methods:**

This study adopts a pilot trial and cluster randomized controlled trial design, with random assignment conducted at the ward level. In the intervention group, units are granted access to AI diagnostic results, while the control group continues standard care practices. Consent will be obtained from attending physicians, residents, and advanced practice nurses in each participating ward. Once consent is secured, these health care providers in the intervention group will be authorized to use the CAD system. Intervention units will have access to AI-generated interpretations, whereas control units will maintain routine medical procedures without access to the AI diagnostic outputs.

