## Methods

### Research Design

This study adopts a 2-phase design, beginning with a pilot study followed by a multicenter cluster randomized clinical trial. The pilot phase focuses on integrating a CXR CAD system into the hospital’s medical information systems, ensuring smooth functionality within the clinical workflow. The system will undergo testing and initial evaluations in the emergency intensive care and ICU at NTUH over a period of 6 to 12 months.

Building on the pilot phase, the multicenter clinical trial involves ICUs from NTUH, FJCUH, and MSGH. A total of 18 ICU units will participate, with NTUH contributing 14 units and the remaining hospitals contributing 2 units each. These units will be randomized into AI-assisted and control groups. Stratification is based on ventilator use, with randomization conducted within each stratum using uniform distribution. The AI-assisted group allows physicians to access real-time predictions from the CAD system during patient care. These predictions, generated within seconds, focus on identifying critical conditions, such as NGT misplacement, ETT misplacement, and pneumothorax. However, physicians in the control group will adhere to standard procedures without viewing AI-generated predictions, though the CAD system will still analyze images for internal validation. To minimize potential bias, both the outcome assessors and data analysts will remain blinded to group allocation throughout the data collection and statistical analysis phases.

The primary outcome is patient all-cause mortality rate: Assess whether the in-hospital mortality rate decreases after the intervention, reflecting the AI-assisted detection system’s ability to identify life-threatening conditions in a timely manner and facilitate rapid clinical intervention.

The secondary outcomes are as follows:

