### Determination of Sample Size

The primary outcome of the trial is to assess whether the CAD system can reduce in-hospital mortality. On the basis of data from the NTUH institutional database [19], the ICU mortality rate in 2023 to 2024 is estimated at 28%. A projected reduction to 25% was used for the sample size calculation. With an intraclass correlation coefficient of 0.01, a power of 80%, and a 1-sided α of 5%, each group requires 5450 patients, resulting in a total sample size of 10,900. This design is expected to provide sufficient power to detect clinically significant improvements in patient outcomes (Figure 3).

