**Figure 3 figure3:**
[figure not shown]
Illustration of study design. AI: artificial intelligence; FJCUH: Fu Jen Catholic University Hospital; ICU: intensive care unit; NTUH: National Taiwan University Hospital.

Because the causes of death in patients admitted in ICU may not necessarily be related to CXRs, adjustments to the primary outcome of the formal trial will be made following the pilot testing. This will involve evaluating and modifying the primary outcome (eg, time to detection of misplacement) to better align with the trial’s objectives and needs.

The conduct and reporting of the trial follow the CONSORT (Consolidated Standards of Reporting Trials) 2010 statement with the extension to cluster randomized trials [20].

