#### Phase 2: Cluster Randomized Controlled Trial

Building on the results of phase 1, this phase will expand to include the ICUs of FJCUH and MSGH, conducting a cluster randomized controlled trial from January 1, 2026, to December 31, 2027, to evaluate the practical application of the CAD system in a multicenter setting, as well as to assess clinical and economic benefits. In addition, the attending physicians, residents, and specialized nurses in the ECC and ICUs will sign consent forms, which will allow them to use the CAD system. Patients will be exempted from providing informed consent, as the study poses minimal risk, and the potential risks for participants are no greater than those for nonparticipants. Exempting informed consent will not affect their rights. The inclusion and exclusion criteria are shown in Textbox 2.

The study will use cluster randomization, stratified by ventilator use frequency, to balance the risk of pneumothorax between the 2 groups and reduce potential confounding bias. Within each stratum, the ventilator use will be similar, while the difference in use between strata will be larger. A uniform distribution will be applied to assign each ward unit a random probability. On the basis of these probabilities, the units will be ranked and assigned to either the intervention or control group based on their odd or even rank.

In the control group, physicians will continue with the current diagnostic process and will not be able to view the model’s predictions. In the intervention group, physicians will be authorized to access the AI model’s predictions during patient care as an additional decision-making reference. These predictions will be generated in seconds and can help identify issues such as tube misplacement (eg, NGT and ETT) and pneumothorax through AI analysis of CXRs, which will alert the physician to review the images. Access to the model’s prediction interface was restricted to physicians in the intervention group, with access for the control group technically disabled through role-based permissions within the hospital information system. This measure ensured that physicians in the control group were not exposed to any AI-generated outputs. In addition, to promote consistent use of the CAD system within the intervention group, log-in records will be monitored, and reminders will be issued in cases of noncompliance.

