### Statistical and Cost-Effectiveness Analysis

Statistical analysis will be conducted using SAS software (SAS Institute) to evaluate the outcomes of this study. Continuous variables, such as clinical outcomes and procedural times, will be summarized using descriptive statistics, including the number of observations, mean, median, SD, range, and 95% CIs. For categorical variables, frequency counts and percentages will be used to summarize the data.

In terms of clinical effectiveness, the primary outcome will be in-hospital mortality, and a proportional test will be used to compare the mortality rates between ICUs that have implemented the AI-assisted detection system and those that have not. The secondary clinical outcomes, which include the length of stay in the hospital, time to detect tube misplacements, and the time taken for medical interventions (such as repositioning of ETT and NGT and placement of pneumothorax drainage), will be analyzed using *t* tests for continuous variables. For categorical outcomes, including the rates of misplacement and other related interventions, chi-square test will be used. In addition, proportional tests will be conducted to examine the differences in the frequency of interventions across the 2 groups.

The study will also incorporate a health care technology and economic evaluation framework to assess the cost-effectiveness of the AI system alongside its clinical effectiveness. This evaluation will explore whether the clinical benefits derived from the AI system justify the associated resource consumption. Previous research by the team [21], such as the use of Markov models in gastric cancer screening and prevention, has demonstrated the utility of such economic evaluations, particularly in quantifying the cost-effectiveness of medical interventions and their impact on mortality reduction.

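### The named primary test for mortality makes no allowance for the 18 randomised units; at the plan's own ICC its 1-sided 5% error is about 27%

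*Protocol article*

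**What the plan says.** **Design.** The abstract describes a cluster randomised trial "with random assignment conducted at the ward level". Research Design adds: "A total of 18 ICU units will participate, with NTUH contributing 14 units and the remaining hospitals contributing 2 units each". Under Phase 2, units are stratified by frequency of ventilator use. Within strata each unit receives a random number, and "the units will be ranked and assigned to either the intervention or control group based on their odd or even rank".

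**Sample size.** Determination of Sample Size takes mortality of 28% against 25%, 80% power and a 1-sided α of 5%. It arrives at 5450 patients per group, 10,900 in all, "With an intraclass correlation coefficient of 0.01". The same section says that conduct and reporting follow the CONSORT "2010 statement with the extension to cluster randomized trials".

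**Analysis.** For the primary outcome, Statistical and Cost-Effectiveness Analysis says that "a proportional test will be used to compare the mortality rates between ICUs that have implemented the AI-assisted detection system" and those that have not. Length of stay and the time outcomes get t tests. "For categorical outcomes, including the rates of misplacement and other related interventions, chi-square test will be used", and further proportional tests compare how often interventions occur. The section mentions neither the unit, the ICC nor the strata.

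**The concern.** The design and the sample size both recognise that patients in one ICU resemble each other. The named analysis does not. A standard test of two proportions takes its standard error from the number of patients, as if each patient had been randomised separately. Here the chance element lies in which ICUs fell into which arm, and there are only about nine per arm.

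At ICC 0.01 and 28% mortality, the standard deviation of true mortality between units is √(0.01 × 0.28 × 0.72) = 0.045, or 4.5 percentage points. The effect sought is 3 points. Ordinary differences between two sets of nine ICUs could therefore be declared a mortality benefit of the detection system far more often than 5% of the time. Mortality is also one of the effect measures in the cost-effectiveness ratio, so a false result would carry into the economic conclusion.

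**Working it through.** **Inputs.** From Determination of Sample Size: p1 = 0.28, p2 = 0.25, ICC = 0.01, 1-sided α = 0.05, power 80%, 5450 per group. From Research Design: 18 units, taken as 9 per arm. Equal unit sizes are an assumption, since the article gives no unit sizes.

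**1. The plan's own sample size.** Without clustering, n per arm = [z₀.₉₅√(2p̄q̄) + z₀.₈₀√(p1q1 + p2q2)]² / (p1 − p2)². With p̄ = 0.265 this is [1.645 × 0.6241 + 0.842 × 0.6238]² / 0.03² ≈ 2675.
- The stated 5450 implies a design effect of 5450/2675 = 2.04. At ICC 0.01 that means 1 + 1.04/0.01 ≈ 105 patients per unit, or about 10,900/105 ≈ 104 units.
- With a continuity correction, n is 2742. At 100 patients per unit this gives 2742 × 1.99 ≈ 5457, close to 5450.
- So 5450 can be approached only with units of about 100 patients. It does not follow from 18 units.

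**2. Design effect with 18 units.** m = 10,900/18 = 605.6. DE = 1 + (605.6 − 1) × 0.01 = 7.05, and √DE = 2.654. For mortality, the unadjusted standard error is too small by that factor.

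**3. True error of the unadjusted test.** 1 − Φ(1.645/√DE) = 1 − Φ(1.645/2.654) = 1 − Φ(0.620) = 0.268.

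| True ICC | DE | True 1-sided error |
|---|---|---|
| 0.001 | 1.60 | 9.7% |
| 0.002 | 2.21 | 13.4% |
| 0.005 | 4.02 | 20.6% |
| 0.01 | 7.05 | 26.8% |
| 0.02 | 13.09 | 32.5% |

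**4. Simulation check.** Beta-binomial data with no effect were generated (9 units per arm, 606 patients each, ICC 0.01, 100,000 runs). The unadjusted 1-sided test rejected in 26.5% of runs. A t test on the 18 unit proportions (16 df) rejected in 5.0%. With unequal units (coefficient of variation 0.5, assumed), the figures were 28.2% and 5.0%.

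**5. Power of a valid analysis.** The effective sample size per arm is 5450/7.05 = 774. Power for 28% versus 25% is then about 38% by the normal approximation, and about 36% for the unit-level t test with 16 df. Adding patients to the same units cannot repair this: with 9 units per arm the effective size cannot exceed 9/0.01 = 900 per arm, against the 2675 needed. At ICC 0.01, 80% power needs more than 2675 × 0.01 = 26.75 units per arm.

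**The case against.** The best defence has four parts.

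- **The unit of analysis is not stated.** The section speaks of comparing rates between ICUs, and the data list includes ward-level items. A t test on unit summaries would be valid, so one cannot say that every planned test is wrong. This stands for the t tests. It is weak for the primary test: the sample is counted in patients, a test of proportions works on patient counts, and no unit-level summary is described. The patient-level reading is still an inference, though the natural one.
- **The CONSORT cluster extension is cited, and a fuller plan may specify an adjustment.** That mitigates, but it is a general statement on conduct and reporting. The article is not silent on the primary test; it names one, and that test does not fit the design.
- **The 27% is conditional.** It needs a true ICC of 0.01 and roughly equal units, and stratification could remove some between-unit variance. This is correct, and it is why a range is given. The inflation is still material at one-tenth of the planned ICC.
- **The primary outcome may change after the pilot**, for example to time to detection. The analysis section would then apply a t test, again with no stated allowance for units.

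Three stronger readings are not supported:

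- A reader might infer from the reference to ICUs that have implemented the system that groups are formed by use and not by allocation. Phase 2 assigns units to groups, disables access in control units and monitors log-ins in intervention units. Nothing describes grouping by use.
- A reader might carry the 7-fold variance over to every outcome. It holds for mortality only. The time outcomes arise only in patients with a misplaced tube or pneumothorax, and no ICC is given for them.
- A reader might blame the missing strata for the inflation. Ignoring strata used in randomisation usually makes a test conservative; the inflation comes from ignoring the units.

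**Conclusion.** The primary analysis is wrong as written. If the test of proportions is run on patients, the nominal 1-sided 5% error for mortality is about 27%, and intervals for the mortality difference are about 2.65 times too narrow. These figures assume ICC 0.01, about 606 patients in each of 18 units, and the 1-sided level in the sample size paragraph (the analysis section restates none). Over ICCs from 0.001 to 0.02 the error runs from about 10% to about 33%. The secondary tests have the same flaw if run on patients, by an unknown amount. A valid analysis controls the error but has about 36–38% power at the planned effect and ICC, against the 80% stated.

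**What to change.** In Statistical and Cost-Effectiveness Analysis, replace the test of proportions with one prespecified cluster-valid comparison of the arms as allocated. Any of these would do:

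- a comparison of the 18 unit mortality proportions adjusted for ventilator-use stratum, using a t distribution with degrees of freedom based on units (18 − 2 − (number of strata − 1));
- a mixed model with a random unit effect, stratum as covariate and a small-sample degrees-of-freedom correction such as Kenward-Roger;
- GEE with stratum as covariate and a small-sample-corrected robust variance. Kenward-Roger does not apply here.

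Apply the same approach to the secondary and cost outcomes. Adjust for pre-trial unit mortality only if it is available for all 18 units. The article cites the NTUH database for one overall rate, and four units belong to other hospitals.

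**Cost.** For the analysis itself, the change is to wording and SAS code, and it can be made before Phase 2 data collection begins in January 2026. The consequence is larger: intervals widen, and the 80% power in Determination of Sample Size must be restated, since 18 units at ICC 0.01 give about 36–38% for 28% versus 25%.

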**Units**
Inclusion criteriaEmergency critical care or intensive care units at National Taiwan University Hospital, Fu Jen Catholic University Hospital, and Min-Sheng General Hospital.The units included the patients requiring chest x-rays due to endotracheal intubation, nasogastric tube insertion, or ventilator use with a risk of pneumothorax.Exclusion criteriaThe unit supervisor does not agree to participate in the trial.The unit is unable to implement the artificial intelligence–assisted system (eg, no data connection or system support).

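### The primary mortality comparison is worded by whether an ICU implemented the CAD system, not by the arm it was randomised to; it should name the allocated arm

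*Protocol article*

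**What the plan says.** All places are in the Protocol article.

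- **How the arms are formed.** Research Design: "A total of 18 ICU units will participate", and "These units will be randomized into AI-assisted and control groups". Phase 2: Cluster Randomized Controlled Trial gives the rule within ventilator-use strata: "the units will be ranked and assigned to either the intervention or control group based on their odd or even rank".
- **How the primary outcome is compared.** Statistical and Cost-Effectiveness Analysis: a test of proportions will "compare the mortality rates between ICUs that have implemented the AI-assisted detection system and those that have not". Later in the same paragraph, a different set of tests is to "examine the differences in the frequency of interventions across the 2 groups".
- **What must happen between allocation and use.** Abstract, Methods: "Once consent is secured, these health care providers in the intervention group will be authorized to use the CAD system". Data Integration Workflow and Ethical Considerations add that ward clinicians must themselves request AI access rights.
- **What is foreseen if use is poor.** Phase 2: "log-in records will be monitored, and reminders will be issued in cases of noncompliance". The same section says that access for control clinicians is blocked by role-based permissions.
- **Unit exclusion.** The unit criteria for the cluster trial (Textbox 2) exclude a unit whose supervisor does not agree, and also one that meets this description: "The unit is unable to implement the artificial intelligence–assisted system (eg, no data connection or system support". Timing relative to the draw is not given.

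**The concern.** Randomisation protects the comparison only if units are compared in the arms to which they were drawn. The sentence on the primary test sorts ICUs by something that happens after the draw. Allocation and implementation can differ here, because going live depends on clinicians consenting and then requesting access. A CAD-allocated ICU in which this never happens fits the literal description of a unit that has not implemented the system.

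Two features make this worth correcting. First, with 18 units there are only about nine per arm, so one unit carries about a ninth of an arm. Second, movement could go one way only: control access is disabled, so a control unit has no matching route to the CAD side. If units that fail to go live tend to have higher mortality than the rest, moving them would flatter the CAD arm. If their mortality tends to be lower, moving them would count against it.

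**Working it through.** **Inputs from the document.** Mortality of 28% without CAD and 25% with it, so a target difference of 28 − 25 = 3 points; ICC of 0.01 (all from Determination of Sample Size). There are 18 units (Research Design), so about nine per arm under the odd/even rule. The article states no figure for non-implementation, so there is none to reproduce. The planned sample size does not enter this calculation.

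**Assumptions, for illustration only.** No true CAD effect; exactly nine units per arm, of equal size; typical units at 28%; in each arm, one unit of a kind that would not implement, with mortality *p* between 31% and 38%. Placing one such unit in each arm represents what randomisation gives on average, so that any difference comes from regrouping and not from chance imbalance.

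**Is that range of *p* plausible?** Reading the ICC on the proportion scale, the between-unit SD is √(0.01 × 0.28 × 0.72) = 0.0449, or 4.5 points. So 31% is 3/4.49 = 0.7 SD above typical, and 38% is 10/4.49 = 2.2 SD above. The upper end is an extreme unit.

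**As randomised.** Each arm has mean (8 × 28 + *p*)/9, so the difference is 0 for every *p*.

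**As implemented, with the CAD-allocated unit moved.** The CAD side has 8 units at 28%. The non-CAD side has 10 units, with mean (8 × 28 + 2*p*)/10. The spurious benefit is 2(*p* − 28)/10.

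| *p* | Non-CAD mean | CAD mean | Spurious benefit |
|---|---|---|---|
| 31% | 286/10 = 28.6% | 28.0% | 0.6 points |
| 33% | 290/10 = 29.0% | 28.0% | 1.0 points |
| 38% | 300/10 = 30.0% | 28.0% | 2.0 points |

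Against the 3-point target this is 0.6/3 = 20% to 2.0/3 = 67%.

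**Variations.**
- Two such units per arm, CAD-allocated ones moved: 4(*p* − 28)/11, which is 1.1 to 3.6 points.
- One unit left out instead of moved: (*p* − 28)/9, which is 0.3 to 1.1 points.
- A unit with lower mortality, say *p* = 25%: 2(25 − 28)/10 = −0.6 points, so the sign reverses.
- Every unit goes live: the two groupings are identical and the effect is zero.

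**The case against.** The strongest reply is that the phrase is simply a loose name for the two randomised arms. Access is tied to allocation, control access is blocked, the economic text speaks of intervention and control arms, and the analysis paragraph itself refers to two groups. That reading is natural and may well be what is meant. It does not remove the problem, because the sentence on the primary outcome is the only one that says who is compared with whom, and its words point to implementation.

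Several stronger readings are tempting, and the article does not support them:

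- *That units change arm or drop out.* No such rule appears. Non-use is met with monitoring and reminders, and malfunction with the usual diagnostic route (Limitations).
- *That a unit with partial use, or one that later stops, would be reclassified.* Such a unit has still implemented the system. Only a unit that never starts is at risk.
- *That the Textbox 2 criteria remove units after randomisation.* They sit under recruitment and read as eligibility. Research Design also has the CAD analysing control-unit images in the background, so a data connection is needed in all units and its absence is not peculiar to the CAD arm.
- *That the lack of an intention-to-treat statement is itself the fault.* An analysis plan or full protocol may contain one. The point rests on what the sentence says, not on what is absent.

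On size, one could place a single CAD-allocated unit 1 SD above average and compare the two groupings: 4.49/9 = 0.50 points against CAD as randomised and 4.49/10 = 0.45 points for it as implemented, a swing of 0.95. That figure should not be used as a measure of bias, because it adds a chance imbalance to the effect of regrouping.

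**Conclusion.** The point holds as a defect of wording in the primary comparison. Taken literally, the sentence would put a CAD-allocated ICU that never goes live on the non-CAD side, and the result would not be the randomised comparison. It cannot be concluded that randomisation is broken or that the investigators intend an as-implemented analysis.

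The illustrated size is 0.6 to 2.0 points in favour of CAD for one such unit per arm, against a 3-point target. It rests on assumed unit mortality, equal unit sizes, no true effect, and a link between non-implementation and higher mortality that the article neither states nor excludes. With no deviating unit it is zero. I rate this a moderate correction, worth making before the planned start of the cluster trial in January 2026, so that the grouping cannot be chosen after the data are seen.

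**What to change.** 1. In Statistical and Cost-Effectiveness Analysis, replace the grouping phrase with wording such as: *In-hospital mortality will be compared between ICUs allocated to CAD and ICUs allocated to control. All eligible patients of every randomised unit will be analysed in the allocated arm, whatever the use of the CAD system.*
2. Beside the unit criteria in Textbox 2, state that supervisor agreement and technical readiness are established for all units before the allocation is drawn.
3. Keep the log-in records for a supplementary analysis by use, labelled as non-randomised.

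**Cost.** These are changes of wording, plus a readiness check before the draw. No extra patients or data are needed and the planned sample size is unchanged. The price is some dilution if units do not use the system: with equal units and a full 3-point effect where it is used, one non-using unit of nine gives 3 × 8/9 = 2.67 points, and two give 3 × 7/9 = 2.33. That smaller figure estimates the effect of allocating ICUs to the system, which is the comparison that randomisation protects.

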Cause-specific mortality rate: a physician panel, blinded to group allocation, will adjudicate the cause of death among study participants. The focus will be placed on respiratory-related mortality, which is most relevant to the conditions targeted by the AI modules.Length of hospital stay: evaluate whether the use of the AI-assisted system shortens hospitalization duration, particularly by enabling earlier detection of tube misplacement and pneumothorax, leading to timely treatment.Time to misplacement detection: determine whether the AI system reduces the time required to identify misplaced tubes or pneumothorax, thereby enhancing the timeliness of clinical interventions.Time to reposition ETT and NGT, and time to place a chest drain for pneumothorax.Direct medical costs (eg, x-ray examinations, intubation fees, and hospitalization costs) and indirect medical costs (eg, CAD system costs and labor costs).

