## Results

The implementation of the AI-assisted CXR CAD system is expected to yield substantial improvements in clinical outcomes and health care efficiency. By enabling timely identification of critical conditions such as misplaced ETT and NGT and pneumothorax, the system is anticipated to reduce in-hospital mortality rates from 28% to 25%. This improvement reflects the system’s potential to facilitate faster recognition of life-threatening situations and prompt clinical interventions.

Moreover, the use of the CAD system is projected to shorten the length of hospital stays, particularly by accelerating the detection of misplaced tubes and pneumothorax, which allows for timely correction and treatment. The time required for specific interventions, such as repositioning ETTs and NGTs or placing drainage tubes for pneumothorax, is also expected to decrease, further enhancing patient care efficiency.

From an economic perspective, the adoption of the CAD system is anticipated to reduce overall health care costs. This includes direct medical costs, such as imaging fees and hospitalization expenses, as well as indirect costs, such as personnel and system maintenance. By improving diagnostic accuracy and reducing delays in treatment, the system is expected to contribute to long-term cost savings while ensuring better health outcomes for patients.

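### Length of hospital stay is compared by t test with shorter read as better and no rule for in-hospital deaths, so the contrast mixes mortality with speed of recovery

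*Protocol article*

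**What the plan says.** In the Protocol article, Research Design lists stay among the secondary outcomes and fixes the favourable direction: "Length of hospital stay: evaluate whether the use of the AI-assisted system shortens hospitalization duration".

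Statistical and Cost-Effectiveness Analysis names the method. The sentence that starts "The secondary clinical outcomes, which include the length of stay in the hospital" goes on to say that these outcomes "will be analyzed using *t* tests for continuous variables". The same section states that "the primary outcome will be in-hospital mortality, and a proportional test will be used".

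On the size of the mortality effect, Determination of Sample Size says that "the ICU mortality rate in 2023 to 2024 is estimated at 28" per cent, and that "A projected reduction to 25% was used for the sample size calculation". The Results section repeats the contrast as an in-hospital one: "the system is anticipated to reduce in-hospital mortality rates from 28% to 25" per cent. It also expects shorter stays.

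The article does not say how a patient who dies in hospital is handled in the stay comparison. It mentions no restriction to survivors, no competing-event analysis and no score or rank for death.

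**The concern.** Death in hospital ends the stay. A short recorded stay can therefore mean quick recovery or early death, and a t test on days in hospital cannot tell them apart. With a death proportion of 25% to 28%, this affects a large share of the data.

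The trial also hypothesises that the device changes the death proportion. The two arms would then differ in their mix of survivors and decedents, and that difference alone can move mean stay without any change in how fast patients recover. Two misreadings are possible. A real shortening among survivors could be hidden or reversed in sign because fewer patients die. Deaths that come sooner would shorten the mean and count as a gain.

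**Working it through.** **Inputs from the article.** Mortality 28% (control) and 25% (intervention); 5450 patients per group; intraclass correlation 0.01; 18 units. The 28% is called ICU mortality in Determination of Sample Size and in-hospital mortality in Results; the point is the same under either label. The 5450 serves here only as an arm size, so nothing below depends on how it was derived.

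**Inputs assumed.** The article gives no mean or SD for stay, so there is no figure of its own to reproduce. Mean stays for survivors (S) and decedents (D) and an SD of 15 to 25 days are assumptions, shown as ranges.

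**Stays ended by death.** Control: 5450 × 0.28 = 1526. Intervention: 5450 × 0.25 = 1362.5, about 1363.

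**Shift from the mortality difference alone.** Mean stay in an arm is (1 − p) × S + p × D, where p is the death proportion. If S and D are the same in both arms, intervention minus control is (0.28 − 0.25) × (S − D) = 0.03 × (S − D).

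| S / D (days, assumed) | Control mean | Intervention mean | Shift |
|---|---|---|---|
| 18 / 14 | 0.72×18 + 0.28×14 = 16.88 | 0.75×18 + 0.25×14 = 17.00 | +0.12 |
| 20 / 12 | 0.72×20 + 0.28×12 = 17.76 | 0.75×20 + 0.25×12 = 18.00 | +0.24 |
| 25 / 10 | 0.72×25 + 0.28×10 = 20.80 | 0.75×25 + 0.25×10 = 21.25 | +0.45 |
| 20 / 20 | 20.00 | 20.00 | 0 |
| 20 / 25 | 0.72×20 + 0.28×25 = 21.40 | 0.75×20 + 0.25×25 = 21.25 | −0.15 |

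**Masking and sign reversal.** Take S = 20 and D = 10. The control mean is 0.72×20 + 0.28×10 = 17.20. If the device truly shortens survivors' stay by 0.25 days, the intervention mean is 0.75×19.75 + 0.25×10 = 17.31. The arm with the real benefit shows a mean 0.11 days longer. Survivors would have to leave 0.30 / 0.75 = 0.40 days sooner just to break even.

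**Earlier deaths at equal mortality.** With 28% dying in both arms, deaths x days sooner in one arm change its mean by −0.28x: −0.28, −0.56 and −0.84 days for x = 1, 2 and 3.

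**Size against noise.** Ignoring clustering, the standard error of the difference is SD × √(2/5450), which is 0.29 days for SD 15 and 0.48 days for SD 25. Shifts of 0.12 to 0.45 days then give z between 0.12/0.48 = 0.25 and 0.45/0.29 ≈ 1.6. If the mortality intraclass correlation also held for stay (a further assumption), the average cluster would be 10,900/18 ≈ 606 and the design effect 1 + 605×0.01 ≈ 7.05. The standard errors become 0.76 to 1.27 days, and z falls to about 0.1 to 0.6.

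**The case against.** Several parts of the case on the other side are sound.

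- **Silence is not a rule.** The article does not say that the t test covers every patient. Restriction to survivors or another death rule might sit in a fuller document. This stands as far as it goes. But the article does fix the test and the favourable direction, and limiting a t test to survivors would compare groups selected by an outcome that the device is meant to change. The named method is therefore a poor choice under either reading.
- **Direction is not known.** A reader might infer that saving lives must lengthen mean stay, so that the comparison is biased against the device by construction. The documents do not support that. The sign follows S − D, and neither figure is given. A patient rescued at the point of death stays longer than otherwise, but an early tube correction could also prevent a long, complicated course that would have ended in death.
- **Costs.** A reader might also infer that bed-day costs in the economic evaluation inherit the fault. They do not. Bed-days used by patients who survive are real costs, and the cost-effectiveness section counts death on the effect side, through mortality and through a QALY weight of zero.
- **Mortality is visible.** In-hospital mortality is the primary outcome and cause-specific mortality a secondary one, so a shorter stay bought with more deaths would be noticed. This safeguard does not reveal earlier deaths when the totals are equal.
- **Mean days is a legitimate measure of resource use.** True. The difficulty lies in reading it as clinical benefit.

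**Conclusion.** The point holds as one of interpretation. A t test on hospital stay, with shorter counted as better and no rule for death, mixes mortality with recovery when about a quarter of stays are expected to end in death and the arms are expected to differ by 3 percentage points. Under assumed stays, the mortality difference alone moves the mean by −0.15 to +0.45 days, and by zero if survivors and decedents stay equally long. Deaths 1 to 3 days earlier at equal 28% mortality shorten it by 0.28 to 0.84 days.

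These figures rest on assumed stays. The direction in the actual trial cannot be settled from the article. Against an assumed SD of 15 to 25 days, the shift from the mortality difference would seldom be significant by itself. The risk is a masked or sign-reversed result on a secondary outcome, which makes this worth correcting but no threat to the primary analysis.

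**What to change.** In Statistical and Cost-Effectiveness Analysis, take stay out of the t-test list. Analyse it as time to discharge alive with in-hospital death as a competing event, allowing for clustering by ICU. Patients who die then count as never discharged alive, so an earlier death cannot pass for an earlier discharge. Hospital-free days to a fixed day, with death scored as zero, is an alternative if follow-up data allow it. Report raw stay descriptively for survivors and decedents separately, next to mortality. Leave observed bed-days unchanged in the cost analysis.

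Cost: the estimate is less intuitive than a difference in mean days. Stay and vital status at discharge must be held per patient. The Phase 2 data list names mortality rate and length of stay but no dates, so a reader should not assume that admission, discharge and death dates are already captured; this needs confirming. No extra patients or procedures are required, and the wording can be settled before the cluster trial's planned start in January 2026.
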